# Effect of physical therapy on breast cancer related lymphedema: protocol for a multicenter, randomized, single-blind, equivalence trial

**DOI:** 10.1186/1471-2407-14-239

**Published:** 2014-04-03

**Keywords:** Manual lymphatic drainage, Complete Decongestive Therapy, Breast cancer

## Abstract

**Background:**

Physical therapy treatment of patients with lymphedema includes treatment based on the principles of ‘Complete Decongestive Therapy’ (CDT). CDT consists of the following components; skin care, manual lymphatic drainage, bandaging and exercises. The scientific evidence regarding what type of treatment is most effective is sparse. The objective of this study is to investigate whether CDT is equally effective if it includes manual lymphatic drainage or not in the treatment of arm lymphedema among patients with breast cancer.

**Methods/Design:**

A randomized, single-blind, equivalence trial. A total of 160 breast cancer patients with arm lymphedema will be recruited from 3 hospitals and randomized into one of two treatment groups A: Complete Decongestive Therapy including manual drainage or B: Complete Decongestive Therapy without manual lymphatic drainage. The intervention period will be approximately 4 weeks followed by a 6 month follow-up period (7 months from baseline). Primary outcome variable: the percentage volume reduction of lymphedema (%) from baseline to 7 months. Secondary outcome variables: Differences from baseline to week 4 and from week 4 to month 7 in circumference of the arm (cm), body weight (kg), patient sensation of heaviness (scale range: 0–10), patient sensation of tension (scale range: 0–10), and quality of life (EQ-5D-5 L-questionnaire).

All measurements are standardized and will be performed before randomization, after 4 weeks and after 7 months.

**Discussion:**

This randomized controlled study seeks to provide data on an effective treatment for patients with breast cancer related arm lymphedema and which at the same time causes minimal patient inconvenience.

**Trial registration:**

ClinicalTrials.gov: Identifier NCT02015897

## Background

Breast cancer is the most common type of cancer in women and in 2011, 4607 women in Denmark were diagnosed with breast cancer [1]. One of the well-known complications of breast cancer treatment is secondary lymphedema; an accumulation of protein-rich interstitial fluid due to the insufficient capacity of the lymphatic system. Axillary lymph-node dissection and subsequent radiation therapy are the most common causes of arm lymphedema [2,3]. The incidence of lymphedema as a sequelae to breast cancer treatment ranges from 6-50%, depending on the surgical procedure in the axilla and the type of the radiation therapy [2,4]. The reported prevalence relies among other things on the definition of lymphedema and which techniques are used to measure it [5]. Lymphedema occurs most often within the first year following the treatment [6,7] and 77% of the patients develop lymphedema within the first three years post-surgery [8].

Lymphedema is a chronic condition and when untreated, the risk of worsening of the lymphedema over time in terms of volume and stage of tissue fibrosis increases [9-11]. In addition to the cosmetic deformities, lymphedema causes impaired physical mobility, mental discomfort, social isolation [12], reduced quality of life [12,13] and higher incidence of erysipelas [12,14].

Physical therapy treatment of patients with lymphedema is based on the principles of ‘Complete Decongestive Therapy’ (CDT). CDT consists of the following components; skin care, manual lymphatic drainage, bandaging and exercises. Traditionally, the bandages used in CDT have been short-stretch bandages. In Denmark, the most commonly used manual lymphatic drainage method is described by Földi [15-17]. The treatment is based on manual lymphatic drainage 4–5 times weekly and each treatment takes 30–45 minutes. However, standardization between different treatment locations and among treating physiotherapists does not exist.

The scientific evidence regarding what type of treatment or combination of treatments is most effective is sparse. Studies [2,3,7,14] have focused on time-consuming manual lymphatic drainage, but the scientific evidence is not consistent [18-20]. The lack of robust evidence may be a contributory cause to the variation of available treatment options among different treatment locations and among treating physiotherapists.

This includes both the combination of treatment methods used and the time spent on each treatment. Furthermore, the type of bandages used varies. Traditionally, the patients receive the manual lymphatic drainage in combination with the replacement of the bandage i.e. 4–5 times weekly, but a new type of bandage may only require replacement two or three times weekly [21]. Reduced replacement of the bandage leads to fewer manual lymphatic drainage treatments and it is unknown whether use of the relatively new but fairly common bandage, Coban™2 Lite, alone can constitute the treatment.

In a recent systematic review [18], the authors concluded that there was not sufficient scientific evidence supporting the use of manual lymphatic drainage in preventing or treating lymphedema. Furthermore, the authors found that the methodological quality of the studies reviewed was poor and with clinical and statistical inconsistencies between the various studies. Therefore, there is a need for well-designed, high quality studies with follow-up.

The hypothesis of this study is that skin care and guidance of physical activity combined with Coban™2 Lite bandage alone is equally effective as Complete Decongestive Therapy including skincare and guidance of physical activity, manual lymphatic drainage and Coban™2 Lite bandage.

### Objectives

Complete Decongestive Therapy is equally effective whether it includes manual lymphatic drainage or not in the treatment of arm lymphedema among patients with breast cancer.

## Methods/Design

### Trial design

The study is a randomized, single blinded, equivalence trial aiming to determine whether an applied composite treatment is equally good if one of its components, manual lymphatic drainage, is removed. The design is illustrated in Figure 1.

**Figure 1 F1:**
[figure not shown]
Flow-chart: equivalence trial – lymphedema study.

The intervention period is approximately 4 weeks followed by 6 months follow-up period. Overall length of the study is 7 months. Primary endpoint will be 7 months from baseline.

The patients complete baseline measurements before the randomization.

### Participants

Patients with breast cancer related lymphedema will be recruited from the Hospital of Southwest Jutland, Lillebaelt Hospital, and the Hospital of Southern Jutland. The following eligibility criteria will be used to determine if a patient can be included:

Inclusion criteria

• Breast cancer diagnosis regardless of the date of operation and identified lymphedema

• Ultrasound scanning of the axilla in order to exclude local relapse

• Lymphedema > 2 cm and stage II-III [22]

• Completed radiotherapy and/or chemotherapy at least 2 months prior to inclusion

Exclusion criteria

• Relapse of breast cancer

• Untreated infection

• Untreated heart failure

• Untreated renal failure

• Untreated deep venous thrombosis in the arm

• Inability to participate in physical therapy treatments and/or inability to understand the instructions

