### Study endpoints and assessments

*Primary outcome measure*: The percentage volume reduction of arm lymphedema (%) from baseline to 7 months.

*Secondary outcome measure*: Differences in circumference of the arm (cm), bodyweight (kg), patient sensation of heaviness (scale range: 0–10), patient sensation of tension (scale range: 0–10), and quality of life (EQ-5D-5 L-questionnaire).

Percentage volume reduction of arm lymphedema (%) from baseline to week 4.

Percentage volume reduction of arm lymphedema (%) from week 4 to week 7.

Length of treatment period until stable circumference of the arm (days).

All measurements are standardized and will be performed before randomization, after approximately 4 weeks and after 7 months (Table 1).

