### Sample size

The margin of equivalence, Δ, was defined as less than 12% points and the range -12% to +12% points thus is predefined as an acceptable range of imprecision (i.e., 95% confidence interval). This margin is based on clinically and statistically important differences as well as ethical criteria, cost and feasibility. In a two one-sided tests (TOST) analysis for additive equivalence of two-sample normal means with bounds -12 and 12 for the mean difference and a significance level of 0.05, assuming a null difference and a common standard deviation of 25%, a sample size of 76 patients with arm lymphedema per group is required to obtain a power of at least 0.8. It was decided to enroll 160 patients in the intention-to-treat (ITT) population. Secondarily to explore a potential difference between the groups, including 160 patients with a two-sided significance level of 0.05, assuming a common SD of 25%, a sample size of 80 per group has a power of 85.5% to detect a mean difference of 12% points.

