### Randomization and allocation concealment

After the baseline assessment, the participants will be randomly assigned to either treatment A or treatment B. The randomization sequence will be created using SAS (SAS 9.2) statistical software stratifying patients by center with a 1:1 allocation using random block sizes of 2, 4 and 6. The allocation sequence will be concealed from the researcher enrolling and assessing participants in sequentially numbered, opaque, sealed and stapled envelopes. Aluminum foil inside the envelope will be used to render the envelope impermeable to intense light.

The patients will be randomized (1:1) in one of the 2 groups:

1. Treatment-group A: standard treatment offered at the hospital containing skincare, manual lymphatic drainage, bandaging and guidance on physical activity.

2. Treatment-group B: standard treatment except for the manual lymphatic drainage. The treatment will include skin-care, bandaging and guidance on physical activity.

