### Statistical analyses

All data analyses will be carried out according to a pre-established analysis plan and all analyses will be done using SAS software (v. 9.2; SAS Institute Inc., Cary, NC, USA). All descriptive statistics and tests will be reported in accordance with the CONSORT statement for non-inferiority/equivalence trials [26], which is the recommendation of the “Enhancing the QUAlity and Transparency Of health Research” (EQUATOR) network [27]. In order to evaluate the empirical distributions of the continuous outcomes, visual inspection of the studentized residuals will be applied to evaluate whether the assumption of normality is reasonable.

Baseline demographic and clinical characteristics will be reported descriptively for all patients in the full analysis set.

The primary analyses will be based on the ‘full analysis set’ , referred to as the intention-to-treat (ITT) population. Missing data following baseline measurements will be replaced using a non-responder imputation (i.e., baseline observation carried forward) [28]. For assessments of change from baseline, analyses of covariance (ANCOVA) will be applied, with treatment assignment serving as the main factor and the baseline value as covariate. Point estimates and 95% confidence intervals (95% CIs) will be provided for the difference in adjusted mean change from baseline between the two treatment groups.

For the discrete (dichotomous) data, the estimate of the proportion of responders (with 95% CIs) within each treatment group, as well as the 95% CIs for the difference in response rates between treatment groups, will be presented.

Equivalence approach to analysis set: In order to demonstrate equivalence the entire 2-sided 95% CI lies within -12% points and +12% points. Thus, the per-protocol population, which includes the subset of patients from the ITT population who had no relevant protocol deviations, will be used to confirm the primary efficacy (equivalence) end point.

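### Lymphedema stage (II or III) is judged for entry but is neither listed in Table 1 nor in the stated ANCOVA, so any precision it could add beyond the baseline value is given up; an optional, almost free improvement, not an error.

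*Protocol article*

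**What the plan says.** Under Participants, the protocol article lists "Lymphedema > 2 cm and stage II-III [22" among the inclusion criteria. The Background treats stage as an aspect of disease severity: in untreated lymphedema, it says, "the risk of worsening of the lymphedema over time in terms of volume and stage of tissue fibrosis increases". On timing, the text beside Figure 1 says "The patients complete baseline measurements before the randomization".

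Stage is not mentioned after the inclusion criteria. Table 1 has baseline rows for age, height and the outcome variables, but none for stage. Randomization is done by "stratifying patients by center with a 1:1 allocation using random block sizes of 2, 4 and 6". Under Statistical analyses, change from baseline is analysed by ANCOVA, "with treatment assignment serving as the main factor and the baseline value as covariate".

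The primary outcome is "The percentage volume reduction of arm lymphedema (%) from baseline to 7 months". The decision rule is stated as "In order to demonstrate equivalence the entire 2-sided 95% CI lies within -12% points and +12% points".

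**The concern.** The trial succeeds or fails on the width and position of one confidence interval, so a baseline factor that predicts the outcome has direct value. Stage may be such a factor. The Background names volume and fibrosis stage as two aspects of worsening, and a more fibrotic arm might lose a different percentage of its volume under either treatment. If so, baseline volume would pick up only the part of stage that goes with size. The rest would stay in the residual variance, although each site has to judge stage anyway in order to apply the entry criterion.

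At stake is a somewhat wider interval than necessary, and hence a somewhat smaller chance of concluding equivalence when the treatments are in fact equivalent.

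**Working it through.** **Inputs from the article (Sample size, Statistical analyses).** Margin ±12 points; common SD 25; true difference 0; two one-sided tests at 0.05; 76 per group required and 80 per group enrolled; decision by the two-sided 95% CI.

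**Inputs not in the article (assumed).** The share of outcome variance that stage explains beyond the baseline value, R²; the share of patients in stage III, p; the difference in mean percentage reduction between stages, d.

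**Step 1: the plan's own figures.** Exact equivalence power with t critical values, "with bounds -12 and 12 for the mean difference and a significance level of 0.05", is 79.98% at 75 per group and 80.7% at 76. The stated 76 is reproduced. The secondary superiority power at 80 per group comes out at 85.5%, also as stated.

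**Step 2: starting point under the stated decision rule.** A two-sided 95% CI corresponds to 0.025 per side. The standard error with 80 per group is 25 × √(2/80) = 3.95. The normal approximation gives 2Φ(12/3.95 − 1.96) − 1 = 71.8%; the exact calculation gives 71.0%. At 0.05 per side the same 80 per group would give 83.2%. The drop from 83.2% to 71.0% therefore comes from sizing at 0.05 and deciding on a 95% CI. Stage plays no part in it.

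**Step 3: effect of adding stage.** Residual SD = 25 × √(1 − R²). The baseline value is given no credit for reducing the SD of 25. The CI half-width is t × SD × √(2/80), and power is the exact figure at 80 per group.

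| Assumed R² | Residual SD | 95% CI half-width | Power, 95% CI rule |
|---|---|---|---|
| 0 | 25.00 | 7.81 | 71.0% |
| 0.01 | 24.87 | 7.77 | 71.7% |
| 0.02 | 24.75 | 7.73 | 72.3% |
| 0.05 | 24.37 | 7.61 | 74.4% |
| 0.10 | 23.72 | 7.41 | 77.8% |
| 0.16 | 22.91 | 7.16 | 81.7% |

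**Step 4: what such R² values would require.** If stage shared nothing with the baseline value, R² = p(1 − p)d²/625:

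- p = 10%, d = 5: 0.1 × 0.9 × 25/625 = 0.004
- p = 10%, d = 10: 0.1 × 0.9 × 100/625 = 0.014
- p = 20%, d = 10: 0.2 × 0.8 × 100/625 = 0.026
- p = 20%, d = 15: 0.2 × 0.8 × 225/625 = 0.058
- p = 20%, d = 20: 0.2 × 0.8 × 400/625 = 0.102
- p = 50%, d = 20: 0.5 × 0.5 × 400/625 = 0.16

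Whatever stage shares with baseline volume has to be deducted from these. An R² near 0.10 needs a large gap between stages; modest gaps give 0.01 to 0.05.

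**Step 5: chance imbalance is not an extra cost.** Take p = 20% and d = 20. The between-stage variance is 0.2 × 0.8 × 400 = 64. The difference between arms in the stage III share has SD √(2 × 0.16/80) = 0.063, which moves the unadjusted difference with variance 0.063² × 20² = 1.6. The unadjusted sampling variance is 625 × 2/80 = 15.625, and the stage part of it is 64 × 2/80 = 1.6, the same quantity. The reported CI already covers it.

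**The case against.** The strongest reply is that nothing here is wrong. Leaving a prognostic factor out of a randomized comparison yields an unbiased estimate and a valid CI. The SD of 25 enters a plain two-sample calculation without covariates, so it is a total SD, and nothing suggests that stage differences were excluded from it. All of this stands.

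A reader might infer that omitting stage is why power is about 71% rather than at least 80%. The article does not support that: Step 2 traces the gap to the two significance levels. A reader might also infer that stage III is known to respond less. No section says so, the staging source is cited but not at hand, and the Background sentence that names volume and stage together could equally point to overlap between them. Nor does the article show that stratification by center alone is a fault. Stratifying by stage without adjusting for it would not narrow the reported CI.

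Two practical objections carry some weight. The entry criterion only requires a patient to fall within the II-III band, so the two grades may not be noted separately or graded alike at three sites. And the article refers to a pre-established analysis plan that is not shown and might add covariates. Against this, the article does name the model terms and the variables assessed, and stage is in neither list. That leaves room for a suggestion, not for a charge of omission.

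**Conclusion.** The point holds as an optional improvement in precision. Stage is needed for eligibility but is absent from Table 1 and from the stated model. Adding it could shorten the 95% CI half-width from 7.81 to 7.73, 7.61 or 7.41 points for R² of 0.02, 0.05 or 0.10. That is worth about 1, 3 or 7 percentage points in the chance of showing equivalence. If stage III is rare, responds like stage II, or is largely captured by baseline volume, the gain is close to nil.

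These figures rest on SD 25, a true difference of zero, 80 analysed patients per group and an assumed R²; the article gives neither the stage mix nor the response by stage. Only a strong stage effect (R² of about 0.15 or more) would bring power to 80% under the 95% CI rule. Stage adjustment should therefore not be presented as the remedy for the mismatch between the sample size calculation and the decision rule, which needs its own resolution.

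**What to change.** Add a baseline row to Table 1 for lymphedema stage, recorded as II or III. Under Statistical analyses, name stage as a fixed covariate beside treatment and the baseline value in the ANCOVA, and settle this before any outcome data are seen by arm so that the choice cannot look data-driven. If the analysis plan already does this, align the article's wording with it.

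The cost is one table row, one model term and one degree of freedom, plus asking sites to note which of the two stages they judged. No patients or visits are added, and stratification need not change.

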### Intervention

#### Treatment groups

The treatment of the patients will be conducted at the departments of physical therapy, Hospital of Southwest Jutland (Esbjerg), Lillebaelt Hospital (Vejle), and the Hospital of Southern Jutland (Aabenraa). The treatment will be performed by lymphedema physiotherapists.

The number of patients included in the study is expected to be equally distributed between the 3 centers. The patients will be randomized into two treatment groups at each treatment site. The intervention period for both groups will be minimum 2 weeks. In approx. three weeks, the lymphedema is expected to be treated to a stable condition estimated by circumference measurements. The circumference of the arm will be measured at seven different locations on the arm at each treatment (twice a week). When two consecutive measurements are stationary (< 0.5 cm difference in three out of five measurements), the active treatment period will end and a permanent and individually tailored compression sleeve/garment will be ordered. The treatment will continue until the sleeve is made and can be given to the patient.

##### Treatment group A

The treatment group A will receive CDT-treatment as offered today at the Hospital of Southwest Jutland, Esbjerg. The treatment includes:

• Skin care

• Manual lymphatic drainage

• Bandaging using Coban™2 Lite

• Guidance on physical activity

The patients will receive the manual lymphatic drainage for 30 minutes twice a week. Total treatment time for each CDT-treatment session will be one hour.

##### Treatment group B

Treatment for group B includes:

• Skin care

• Bandaging using Coban™2Lite

• Guidance on physical activity

Treatment time for each session will be 30 minutes and will be given twice a week.

All measurements and questionnaires will be performed before randomization, after approximately 4 weeks and after 7 months (Table 1). The measurements will be performed by non-treating personnel.

**Table 1 T1:** Outcomes and variables assessed during the trial period

**Variable**	**Baseline visit 1**	**4 weeks visit 2**	**7 months visit 3**
Age	X		
Body height,cm	X		
Arm lymphedema volume, ml	X	X	X
Circumference of the arm, cm	X	X	X
Body weight, kg	X	X	X
Sensation of heaviness, score	X	X	X
Sensation of tension, score	X	X	X
Quality of life (EQ-5D-5L), score	X	X	X

#### Specification of each treatment component

##### Skin care

In order to maintain the integrity of the skin, at each treatment the arm is bathed and treated with softening and unscented lotion.

##### Manual lymphatic drainage

Manual lymphatic drainage aims to remove excess interstitial fluid and increase lymphatic transport. The treatment method used is according to descriptions by Földi [15-17]. The manual lymphatic drainage is a gentle massage and the movements are slow and rhythmical. The method consists of 4 basic techniques with a pressure phase and a relaxation phase.

##### Bandaging

Coban™2 Lite is a two-component compression system with a comfort layer close to the skin and a self-adherent external compression layer. The comfort layer is applied with minimal overlap and without tension whereas the compression layer is applied with 50% overlap and at full stretch, corresponding to a pressure of approximately 30 mmHg. The bandage is retained until the next treatment.

##### Guidance on physical activity

In order to maintain/increase the mobility, the patients are encouraged to maintain normal function and information about the muscle pump is provided.

### Guidance of sleeve treatment in the observation period

The sleeve is considered to be a permanent assistive device and when given to the patients, they will be instructed in applying the sleeve. Additionally, it will be recommended that they keep the sleeve on every day from morning till night.

